### Aim/objectives and research questions (RQ)

The aim of this project is to evaluate the consequences of parental leave policy in Sweden from a health equity perspective. More specifically, the project will cover the following RQ:

RQ#1: Is eligibility for earnings based parental leave benefits associated with parents’ mental health?

RQ#2: Is short birth spacing in relation to the speed premium supplement reform associated with health problems in the subsequent pregnancy of the mother (early pregnancy obesity) and the subsequent child (low birth weight, preterm and small-for-gestational age)?

RQ#3: Does the introduction and expansion of the father’s quota reserve days influence the mental health of parents after the birth of their child?

RQ#4: Does the introduction of simultaneous parental leave use through the double days reform influence parents’ mental health?

RQ#5: Does the introduction of the father’s quota and double days reforms influence children’s health (episodes of respiratory tract infections, childhood obesity) or health-related outcomes (duration of breast feeding)?

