## Methods and analysis

### Study population

We will include all Swedish-born and foreign-born individuals registered in Sweden between 1973 and 2019 and their Swedish-born children, followed through their first 5 years of life. For most studies, we will focus on a subsample consisting of all women (and their partners) residing in Sweden who had their first birth in the country between 1973 and 2019.

Studies will be primarily focused on primiparous couples, with secondary analyses for multiparous couples. We will only include biological parents, since we aim to examine joint biological and psychosocial consequences of parental leave uptake, with singleton children, given that parents of multiple births are entitled to more days of leave.^6^ Separate analyses by parents’ sociodemographic characteristics, nativity and cohabitation status will be conducted to investigate the heterogeneity of effects in the population.

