### Outcomes

Child health outcomes include low birth weight (<2500 g, irrespective of gestational age), preterm birth (<37 gestational weeks) and a small-for-gestational age measure (<10th percentile of birth weight for each gestational age, based on sex-specific Swedish reference curve for normal foetal growth)^41^ from the MBR; hospitalisation episodes of respiratory tract infections during the first 2 years of life (International Classification of Diseases-10 (ICD-10) Codes J20.5, J21.0, J21.9, J20.9, J18.9, J12.9 and J22.9) from the NPR and duration of partial or exclusive breast feeding (at months 2, 4, 6, 9 and 12) as well as childhood obesity (body mass index (BMI); weight in kilograms/height in meters^2^ using age-specific and sex-specific cut-offs for children’s overweight and obesity^42 43^ at 18 months and 3–5 years) from the CHR. Maternal health outcomes include maternal early pregnancy overweight (BMI 25–29.9 kg/m^2^) and obesity (BMI 30–39.9 kg/m^2^).^44^

Mental health outcomes will be assessed for both parents using count data on purchases of prescription anxiolytic and antidepressant medications (Anatomical Therapeutic Classification Codes N05B and N06A, respectively) as well as outpatient visits and hospitalisations with a primary diagnosis of mental and behavioural disorders (until 1997, ICD-9 Codes 290–319; thereafter, ICD-10 Codes F00-F99), from childbirth to 18 and 36 months after birth.

Outcomes will be expressed as prevalence or rates, given availability of follow-up time.

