### Study design and statistical analyses

A variety of advanced designs and statistical methods for observational data will be applied. First, using descriptive and correlational designs, we will implement standard multivariable methods to quantify links between prebirth health conditions, parental leave eligibility and uptake, and postbirth health outcomes while accounting for confounding using relevant covariates and heterogeneity analyses.

Second, we will use robust quasi-experimental approaches to assess the causal effects of parental leave policy on health, reducing the risk of selection effects and unmeasured confounding by harnessing the natural, ‘as-if’ randomisation around policies.^45 46^ With this approach, we can isolate the absolute policy effects on health even in the absence of detailed information on changes in parental leave uptake. These approaches include interrupted time series (ITS), regression discontinuity (RD) and difference-in-difference (DiD) designs. For ITS designs, segmented regression models will be adjusted for seasonality and trend while accounting for autocorrelation.^46^ For RD designs, continuity around the cut-off will be tested using the McCrary Density Test and similarity of eligible and ineligible observations will be determined through descriptive statistics. Finally, for DiD designs, we will examine the data to confirm parallel trends and other relevant assumptions.^45^

RQ#1: We will examine the effects of the 2002 doubling of flat-rate benefits on the mental health of parents. An RD design will be applied to plot psychiatric hospitalisation rates with labour income as a forcing variable, with separate plots before (with an income cut-off equivalent to 75 SEK, at 80% reimbursement rate) and after 2002 (with a cut-off equivalent to 150 SEK daily). Cut-offs for both parents’ income will be examined. We will triangulate our findings with a DiD approach, comparing those eligible for the increased benefits to those ineligible before and after reforms.

RQ#2: A segmented-regression ITS of monthly birth data comparing the rate of low birth weight and preterm births 3 years before and after the 1980 and 1986 speed premium reforms will be implemented. We will also compare the prevalence of obesity in mothers early in their second pregnancy before and after the reform.

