### Additional analyses

Given the potential for effect modification and compositional changes in the study populations, subgroup analyses by parents’ sociodemographic characteristics (ie, annual labour income, to determine eligibility for earnings based benefits or educational attainment) will be considered for all RQ. Analyses by parents’ nativity will be implemented for RQ#2–4, given differential responses to the policies by Swedish-born and foreign-born parents.^14^ Other relevant parental characteristics, that is, age at childbirth and cohabitation status, will also be considered.

Sensitivity analyses will be performed to account for systematically missing data, such as maternal weight (ie, given that women appearing to be of normal weight are less monitored for obesity).^47^ For studies examining first births, sensitivity analyses restricting mental health outcomes to the 18 months post birth will be considered in order to exclude the potential health effects related to a second pregnancy.

For all ITS designs, we will specify multiple intervention points to assess the possibility of lagged policy effects. Robustness analyses of falsification (‘pseudo-intervention’) dates and falsification outcomes (eg, prebirth hospitalisations) will also be considered.

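### Maternal obesity is capped at BMI 39.9, so as written women with BMI 40 or more do not count as obese in the RQ#2 prevalence comparison

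*Protocol article*

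**What the plan says.** The Outcomes section lists two maternal BMI classes. It opens with "Maternal health outcomes include maternal early pregnancy overweight (BMI 25–29.9 kg/m^2" and continues with "and obesity (BMI 30–39.9 kg/m^2". No third class is given.

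RQ#2, under Aim/objectives and research questions, names obesity as the maternal endpoint: "health problems in the subsequent pregnancy of the mother (early pregnancy obesity". The Study design and statistical analyses section then sets the comparison: "We will also compare the prevalence of obesity in mothers early in their second pregnancy before and after the reform".

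Two other places could have dealt with BMI 40 or more, and neither does. The Study population section restricts by parentage and plurality: "We will only include biological parents, since we aim to examine joint biological and psychosocial consequences of parental leave uptake, with singleton children". It has no restriction on BMI. The Additional analyses section deals with weight only where it is not recorded: "Sensitivity analyses will be performed to account for systematically missing data, such as maternal weight".

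**The concern.** An outcome called obesity would be expected to include every woman at or above its lower threshold. Here it stops at 39.9, so a woman with BMI 41 meets neither maternal definition. The other birth outcomes with numerical cut-offs in the same section (birth weight below 2500 g, birth before 37 weeks, birth weight below the 10th percentile for gestational age) are all open at the severe end. Maternal obesity is not, and no reason is given.

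What is at stake is the only maternal endpoint that RQ#2 names. The Introduction's rationale is that short birth intervals may raise the risk of weight gain and obesity, and the cap removes the heaviest women from the outcome meant to detect this. If the proportion of such women differs between the periods before and after the reform, the contrast itself is affected as well as the level.

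**Working it through.** **The plan's own figure.** The article states no prevalence, sample size or power for this outcome, so there is no figure to reproduce. The check applies the stated ranges literally and then works out the effect on prevalence.

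**Step 1: classification as written.**

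| BMI | Class under the stated ranges |
|---|---|
| 27 | overweight |
| 30, 35, 39.9 | obese |
| 40, 45 | neither |

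**Step 2: effect on the level.** Let P be the true prevalence of BMI 30 or more, and s the share of those women with BMI 40 or more. Both are assumptions, because the article gives neither.

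- If women with BMI 40 or more stay in the denominator: measured = P(1 − s). The relative understatement is exactly s.
- If they are dropped altogether: measured = P(1 − s)/(1 − Ps).

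With P = 5%:

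| s | Kept in denominator | Dropped |
|---|---|---|
| 1% | 4.95% | 4.95% |
| 3% | 4.85% | 4.86% |
| 5% | 4.75% | 4.76% |
| 10% | 4.50% | 4.52% |

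The two handlings differ by at most 0.02 percentage points here, so the point does not depend on which one was meant.

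**Step 3: effect on the before/after contrast** (women kept in the denominator).

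- *s the same in both periods.* Ratio = P₂(1 − s)/[P₁(1 − s)] = P₂/P₁, so the relative contrast is unchanged. Difference = (P₂ − P₁)(1 − s), so the absolute difference shrinks by s. If the women are dropped instead, the ratio is almost unchanged: for P from 5.0% to 5.5% and s = 2%, it is 1.10 × (1 − 0.0010)/(1 − 0.0011) = 1.1001.
- *s different.* The ratio is multiplied by (1 − s₂)/(1 − s₁). For s from 1% to 3% this is 0.97/0.99 = 0.980, a spurious relative fall of about 2%.

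For an assumed true rise from 5.0% to 5.5% (0.50 points) with s = 2% before the reform, the measured value before is 5.0% × 0.98 = 4.90%. Then:

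| s after | Measured after | Measured rise |
|---|---|---|
| 2% | 5.39% | 0.49 points |
| 5% | 5.225% | 0.33 points |
| 10% | 4.95% | 0.05 points |

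The last two rows show how the mechanism behaves under large shifts in s. Nothing in the article suggests that shifts of that size occurred.

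**The case against.** The strongest reply is that the article is condensed, says only that the maternal outcomes include these classes, and cites a source for them that is not available here. A separate class for BMI 40 or more might sit in a fuller document. That is a fair reason for caution about intent, and the cap may be a drafting slip. It does not remove the point: the article gives obesity a stated numerical range, and that range leaves out part of what the term covers. This is a definition as fixed, not a detail left for later.

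Three stronger readings are tempting, and the article does not support them.

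- *That women with BMI 40 or more are analysed as non-obese members of the denominator.* The text does not say how they are handled. They could equally be dropped. What it supports is that they are not counted as obese.
- *That a mother whose BMI goes from 38 to 41 between pregnancies leaves the case group.* No within-woman change is planned for this outcome. The comparison is of prevalence between cohorts of mothers early in the second pregnancy, and BMI in the first pregnancy does not define a case.
- *That any weight gain from short spacing is under-counted.* Gains that cross 30 and stop below 40 are captured in full. Only those that reach 40 or more are missed.

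It is also true that the segmented regression for RQ#2 is specified for low birth weight and preterm birth, with maternal obesity as an additional comparison. Those outcomes and the other research questions are untouched. Childhood obesity uses its own age- and sex-specific cut-offs.

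**Conclusion.** The point stands as an error in an outcome definition. As written, women with BMI 40 or more fall outside both maternal BMI classes and do not count as obese in the RQ#2 before/after comparison.

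The size rests on s, which the article does not give. If s is 1–5%, prevalence is understated by about 1–5% in relative terms. With s stable across the reform, the relative contrast is essentially preserved and the absolute difference loses about the same 1–5%. Real distortion of the contrast needs s to change: a rise from 1% to 3% would add a spurious relative fall of about 2%. The effect is therefore probably small and confined to one outcome. It is worth correcting because it removes the most severe cases from a named endpoint and is easy to put right.

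**What to change.** In the Outcomes section, define maternal early pregnancy obesity as BMI 30 kg/m² or more, with no upper limit. If the heaviest group is of interest, report BMI 40 or more as a subclass within obesity. If the cap was deliberate, for example to screen out implausible register values, state that as a data-cleaning or exclusion rule with its reason, separate from the outcome definition, and apply it identically in both periods.

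The cost is one threshold in the outcome coding. No new data are needed, and no other analysis changes.

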### Data

This project will use data from available national registers, collected and linked by the Swedish authorities. Using a unique personal identity number,^33^ we will identify and reconstruct families in the study population through the total population register (TPR; 1968-)^34^ and the multigenerational register (2001-).^35^ Sociodemographic information will be retrieved from the TPR, the Longitudinal Integration Database for Health Insurance and Labour Market Studies (LISA; 1990-),^36^ the Swedish Social Insurance Agency Database (SIAD; 1955-) and the 1985 and 1990 Population and Housing Censuses. We will link health information from the National Patient Register (NPR), on inpatient (IPR; 1964-)^37^ and outpatient care (IPR; 2001-), and the medical birth (MBR; 1973-),^38^ cause of death (1952-)^39^ and prescribed drug (2005-) registers.^40^ We also plan to include information from the Swedish children’s health centres (1993-), with full coverage of longitudinal childhood obesity and breastfeeding data from the counties of Uppsala and Örebro (see figure 2).

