RQ#3: We will conduct an ITS analysis of parents of children born before and after the 1995 father’s quota reform using segmented regression to capture changes in psychiatric hospitalisation rates up to 36 months after childbirth, based on fathers’ eligibility for the father’s quota.

RQ#4: An ITS for parents to children born before and after the 2012 double days reform will be implemented to capture changes in the number of outpatient visits for mental health and psychotropic prescriptions within 36 months after childbirth, by child’s month of birth.

RQ#5: We will implement separate ITS analyses of children born before and after the 1995 father’s quota and 2012 double days reforms, comparing hospitalisation rates for diagnoses of respiratory tract infections (in children under 2), prevalence of childhood obesity (at 18 months and 3–5 years) and changes in breastfeeding duration.

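### RQ#4 counts all psychotropic purchases and mental-health visits after birth without using pre-birth treatment, which costs precision and leaves a null result hard to interpret

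*Protocol article*

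**What the plan says.** The Outcomes section of the protocol article defines mental health for both parents through "count data on purchases of prescription anxiolytic and antidepressant medications" (ATC groups N05B and N06A), together with "outpatient visits and hospitalisations with a primary diagnosis of mental and behavioural disorders". The counting window runs "from childbirth to 18 and 36 months after birth". The same section adds: "Outcomes will be expressed as prevalence or rates, given availability of follow-up time".

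Under Study design and statistical analyses, RQ#4 is an interrupted time series by the child's month of birth. Its outcome is "changes in the number of outpatient visits for mental health and psychotropic prescriptions within 36 months after childbirth". The question itself, under Aim/objectives, is broad: "Does the introduction of simultaneous parental leave use through the double days reform influence" parents' mental health.

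Pre-birth health appears in two other places:
- The separate descriptive and correlational strand will "quantify links between prebirth health conditions, parental leave eligibility and uptake, and postbirth health outcomes".
- Additional analyses names pre-birth hospitalisations as one example of a falsification outcome that may be considered.

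The subgroups named under Study population and Additional analyses are sociodemographic characteristics, nativity, age at childbirth and cohabitation. The 18-month sensitivity analysis is there to exclude effects of a second pregnancy. None of these separates parents by earlier treatment.

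The Data section lists "prescribed drug (2005-) registers" and outpatient care from 2001.

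**The concern.** The unit is the purchase or the visit, and each one after birth counts equally whenever the treatment began. Suppose a parent on stable treatment since before the pregnancy refills every three months: that parent scores 36/3 = 12. A parent with new illness after the birth, treated for six months at the same interval, scores 6/3 = 2. The total is weighted towards long-standing treatment, part of which began before the reform could act.

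This matters for RQ#4 in particular. The Limitations section turns to the 2012 reform in order to study less severe outcomes. The introduction describes the mechanism as fathers sharing care while mothers recover from birth, and onset or worsening after birth is a natural place to look for such an effect. If most of the count is continuing treatment, a real change in new illness is a small part of what is analysed. The planned output would not show the reader whether a null means no effect or a masked one.

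**Working it through.** The article states no event rate, effect size, power or sample size for RQ#4, so there is no figure to reproduce. Every rate below is an assumption, chosen to show the range.

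**1. Share of purchases from parents already treated.** Let p be the proportion treated before birth, c the proportion of them who continue, n their purchases over 36 months, w the proportion of new users among the untreated, and m the purchases per new user.

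- Continuing part: a = p·c·n. New part: b = (1 − p)·w·m. Share = a/(a + b).
- A 10% fall in new users, with no effect in treated parents, lowers the total by 10% × (1 − share).

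| Scenario | p | c | n | w | m | a | b | Share | Fall seen in total |
|---|---|---|---|---|---|---|---|---|---|
| A | 0.04 | 0.7 | 12 | 0.08 | 5 | 0.336 | 0.384 | 47% | 5.3% |
| B | 0.06 | 0.7 | 12 | 0.08 | 4 | 0.504 | 0.301 | 63% | 3.7% |
| C | 0.03 | 0.6 | 9 | 0.10 | 5 | 0.162 | 0.485 | 25% | 7.5% |

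A wider grid takes 2–8% treated at birth with 4–12 purchases each, and 4–8% new users with 3–5 purchases each:
- Lowest share: 0.02×4 / (0.02×4 + 0.08×5) = 0.08/0.48 = 17%; a 10% fall shows as 8.3%.
- Highest share: 0.08×12 / (0.08×12 + 0.04×3) = 0.96/1.08 = 89%; a 10% fall shows as 1.1%.

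**2. Gain from adjustment alone, keeping the total count.** Take second moments of 1.3n² for continuing users and 2m² for new users. In scenario A:
- Total variance = 0.04×0.7×1.3×144 + 0.96×0.08×2×25 − 0.72² = 5.2416 + 3.84 − 0.5184 = 8.563, about 12 times the mean of 0.72.
- Stratum means are 0.7×12 = 8.4 (treated) and 0.08×5 = 0.4 (untreated).
- Between-stratum variance = 0.04×0.96×(8.4 − 0.4)² = 2.458.
- Within-stratum variance = 8.563 − 2.458 = 6.106.
- Efficiency ratio = 8.563/6.106 = 1.40.

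The same steps give 1.62 in B and 1.12 in C. Adjusting for one yes/no indicator of earlier treatment is thus worth about 1.1 to 1.6 times as many parents, with the outcome unchanged.

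**3. A new-user outcome compared with other outcomes.** This is the ratio of squared z-scores for a 10% fall in new users, in the order A, B, C:
- Binary new use against the total count: 4.8, 8.7, 2.9.
- Part of that due only to replacing a count by yes/no: about 2.1 in each scenario.
- Part due to leaving out treated parents: 2.3, 4.2, 1.4.
- Binary new use against any-purchase prevalence in all parents: 1.33, 1.50, 1.17.

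These are per-parent comparisons with independent observations. They ignore trend, seasonality and autocorrelation in the monthly series, and they assume no effect in treated parents.

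**4. Is a look-back available?** The reform took effect on 1 January 2012. Drug data from 2005 reach back about 2012 − 2005 = 7 years and outpatient data about 2012 − 2001 = 11 years. A window of 12 months before conception plus 9 months of gestation needs 21 months of drug data. The article gives no starting month for 2005, so the first births with a full window fall between about October 2006 (January start) and about September 2007 (December start).

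**The case against.** **RQ#4 does not ask about new onset.** It asks about parents' mental health, so relapse, continuation and intensity of care in people with earlier illness belong to the answer. The introduction names people with long-term illness as an equity concern. This stands. Making new use the main outcome would change the estimand, and it would miss any benefit that falls on parents already in treatment.

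**The design absorbs a stable background.** A reader might infer that continuing refills bias the RQ#4 estimate. The article does not support that. Segmented regression with trend and seasonality takes up a constant or slowly drifting contribution, and the stated target is the absolute policy effect. Bias would need the treated share, or dispensing practice, to shift abruptly with births around January 2012, and nothing in the article suggests such a shift.

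**Prevalence is also allowed.** The Outcomes section permits it, and it scores the parent with 12 refills and the parent with 2 alike. This stands in part: it removes the weight of repeat refills but still counts every continuing user. It also means that the roughly three- to nine-fold advantage of a new-user outcome over the count should not be taken as the cost of the plan. Against prevalence the advantage is about 1.2 to 1.5 times.

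**The size rests on assumptions, and the population is national.** True: inadequate precision has not been shown. A fuller plan may also use earlier treatment. But the article does fix the unit and the window for RQ#4, and the uses of pre-birth health that it names are in the correlational strand or are an optional check of the design. The planned look at population composition is described in sociodemographic terms.

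**Conclusion.** The point holds as a matter of precision and interpretation. The RQ#4 outcome as written does not use pre-birth treatment, and continuing treatment may supply a large but unknown share of it: 25–63% in the three scenarios and 17–89% on the wider grid. With a stable treated share the absolute level change remains unbiased. Relative effects are diluted, so that a 10% fall in new use shows as 3.7–7.5% in the scenarios and 1.1–8.3% on the grid, and a null is ambiguous. Adjustment alone would recover an efficiency gain of about 1.1 to 1.6 times under the scenario inputs. All these figures depend on assumed rates and on no effect in treated parents. The material does not show that the total count is the wrong outcome or that it must be replaced.

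**What to change.** 1. Keep the total count or prevalence as the RQ#4 outcome, and state which of the two leads.
2. Adjust for, and report stratified by, N05B/N06A purchases and mental-health outpatient visits in one fixed window before conception, for example 12 months. Use the same window for births before and after the reform, and start the drug series no earlier than the first birth month with a full look-back.
3. Add one prespecified secondary outcome: the proportion of parents with a first purchase or first visit after birth among those with none in that window.

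The cost is a few more derivations from registers already in the planned linkage and one more reported outcome. Effects in previously treated parents stay visible in their own stratum.
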